### Blinding

Since all assessments take place online, thus in the absence of the researchers, the outcome data are blinded. However, one researcher will be aware of the condition of the participants in order to support them appropriately when technical or personal problems appear. It is unlikely that this will entail problems of bias, as the researcher is not involved in any measurement and the motivational part of the study lies in the responsibility of the therapists. The therapists and participants will be blinded for the two training conditions. Therefore, the iABM intervention and the placebo condition were designed such that the use of the same task stimuli would be possible, making both conditions look very similar. Furthermore, it is unlikely that participants will tell their therapists much about the content of the training, but more about whether they train regularly or whether they like or dislike the training. This will help to keep the therapists blinded. Furthermore, the therapists will be instructed not to do any ‘research’ about what might be the ‘real’ intervention. Participants will be asked to indicate their expectation about their condition in the post-assessment.

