After assignment to the system, all participants will be invited by e-mail to complete the baseline assessment. Participants who are assigned to the TAU-only condition will thereafter receive TAU. Participants who are assigned to one of the trainings (active or placebo) will thereafter read the training instructions. Furthermore, they can watch an animated video in which the training is explained. Hereafter a short 5-min practice session of the training follows. One day after completing the baseline assessment and the practice session of the training, participants in one of the training conditions will receive an invitation for the first training session by e-mail. The following three weeks, participants will be asked to train on a daily basis. Thereafter, the number of training sessions per week will decline. Participants will train three times a week for another three weeks and finally once a week until the end of TAU. Thus, the actual number of training sessions is dependent on the duration of TAU. The lower doses treatment in the Dutch addiction care usually takes 3 to 6 months, depending on the severity and the progress of the patient. During the whole training period a researcher will monitor the process of the patients and whether they train regularly. After three training sessions are missed, patients will receive an automatic reminder by e-mail. If this does not result in the continuation of the training the researcher will contact the patient via the preferred way (phone, e-mail, text message or app) in order to ask whether there are any problems or doubts about the participation in the study.

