An important part of the study is the involvement of the therapists. In order to improve adherence, the researchers will train the therapists before the inclusion of participants starts. The training will consist of the following parts (1) general background knowledge about attentional bias and ABM, (2) design and important parts of the study, and (3) the role of the therapists. During the training all therapists will receive a protocol in which all important aspects are described. In the first session of TAU after patients are assigned to the study, therapists will identify the time of the day patients’ craving is strongest and will instruct the patient to complete the ABM task at this particular time of the day. Furthermore, during each following treatment session of TAU, the therapist will ask the participant whether he/she trains on a regular basis, and will engage in motivational counselling if this is not the case.

During the last week of TAU in addiction care, participants in the training conditions will receive the last training invitation by e-mail. After completion, they will be invited for the post-assessment. Participants in the TAU-only condition will also receive the invitation for the post-assessment in their last week of TAU. Finally, 6 and 12 months after the end of TAU, all participants will receive an invitation for the follow-up measurements by e-mail. In case a participant does not respond to these invitations, the researcher will remind the patient via the preferred way (phone, e-mail, text message or app). Throughout the length of the whole project, a sounding board group will meet four times to monitor the process of the study. The group will include a researcher, a therapist, and a member of the client council of each addiction care centre, and an implementation professional.

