#### Questionnaires

Participants’ general health state is assessed by means of the EuroQol-5D-3 L questionnaire [49]. Health care-related costs are evaluated with the Treatment Inventory of Costs in Psychiatric Patients questionnaire [50]. The Measurements in Addiction for Triage and Evaluation questionnaire [51] is a standard instrument in the Dutch addiction care and will be completed during the intake and at the end of the treatment through the therapists. During the 6 and 12 month follow-up measurements, the same questions will be asked online. For this study, the following parts of the MATE will be evaluated: substance use, the Obsessive-Compulsive Drinking Scale (OCDS5), and the Depression Anxiety Stress Scale (DASS).

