### Primary and secondary outcome measures

The effectiveness of the iABM intervention will be examined by changes in substance use (i.e. quantity of use in the past 30 days), craving, and relapse rates. Measurements of attentional bias will serve as a manipulation check for the effects of iABM intervention.^1^ Secondary outcome measures are cost-effectiveness,^2^ and secondary physical and psychological complaints (depression, anxiety, and stress). The evaluation forms of the patients and therapists will be assessed as well.

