### Randomization

Participants who meet the inclusion criteria will be automatically assigned to one of the three conditions with the following likelihood (1) 50% TAU + iABM, (2) 25% TAU + placebo condition and (3) 25% TAU-only. Furthermore, the registration and monitoring system stratifies for gender, age group (18–30, 30–50, 50+), type of addiction, and institution. Therefore, participants are assigned to one of the three conditions to which the fewest participants of their gender, age group, and type of addiction are assigned accounting for the institution of the participants. When proven effective, participants in the control conditions (TAU + placebo condition and TAU-only) will be offered the iABM intervention after the end of the study (approx. End 2018).

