#### Economic evaluation

If the iABM intervention was shown to be effective, the economic evaluation will be performed from a societal perspective, which means that all relevant costs will be taken into account, regardless of who pays for them. Health-care costs, such as contacts with health care professionals, and costs of lost productivity will be calculated by multiplying the volumes of health-care with standard unit prices derived from the Dutch Manual for cost research [52].

The time horizon of the economic evaluation will be 12 months and will compare the iABM intervention to TAU-only. Cost-effectiveness and cost utility will be assessed by relating the incremental costs of the two treatments to the incremental outcomes. The primary outcome measure in the cost effectiveness analysis will be substance use and relapse rates, as measured with the MATE and additional questions regarding relapse. In addition, a cost utility analysis will be performed with quality-adjusted life years (QALYs) as primary outcome, based on the EQ-5D-3 L defined utilities. No discounting of costs and effects will be conducted, since the time horizon does not exceed 1 year.

Uncertainty surrounding the cost-effectiveness and cost utility ratios will be assessed using bootstrap analysis. In addition, cost-effectiveness acceptability curves will be used to inform decision-makers on the probability that iABM intervention is cost effective.

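### The Blinding section calls the outcome data blinded because assessments are online, but only iABM versus placebo is blinded, and the MATE at intake and end of treatment goes through the therapists

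*Protocol article*

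**What the plan says.** The Blinding section opens its argument with a general statement: "Since all assessments take place online, thus in the absence of the researchers, the outcome data are blinded". It then discusses the one researcher who knows the allocation, and turns to patients and therapists: "The therapists and participants will be blinded for the two training conditions". It says nothing about TAU-only.

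Other sections of the protocol article bear on the claim:

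- **Allocation (Randomization):** "1) 50% TAU + iABM, (2) 25% TAU + placebo condition and (3) 25% TAU-only".
- **What TAU-only receives (Participants and procedure):** "Participants who are assigned to the TAU-only condition will thereafter receive TAU". The training arms instead get instructions, a practice session and e-mailed training invitations.
- **Therapist contact (Participants and procedure):** at each later session, "the therapist will ask the participant whether he/she trains on a regular basis", with motivational counselling for those who do not train.
- **Primary clinical outcomes (Primary and secondary outcome measures):** "changes in substance use (i.e. quantity of use in the past 30 days), craving, and relapse rates".
- **Collection of the MATE (Questionnaires):** it "will be completed during the intake and at the end of the treatment through the therapists", and is asked online only at 6 and 12 months. The MATE supplies substance use, craving and the depression, anxiety and stress scores.
- **Clinical analysis:** each repeated-measures ANOVA sets iABM against the two control conditions combined.
- **Economic evaluation:** it "will compare the iABM intervention to TAU-only".
- **Trial design:** the iABM–placebo comparison is named as the means of controlling for a placebo effect.

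**The concern.** The sentence draws a conclusion that does not follow. An absent researcher cannot influence the answers, but most of these outcomes are the patient's own account, and a patient who knows the allocation is not a blinded source. The three arms differ in this respect, and the sentence makes no exception for any of them.

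Its premise is also contradicted. If the MATE at the end of treatment goes through the therapist, the main clinical outcomes at that visit pass through someone who can tell which patients have no training.

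At stake is how the results will be read. The main clinical contrast mixes a blinded and an unblinded comparator, and the economic contrast uses only the unblinded one. With the sentence left as it is, results on self-reported use, craving or EQ-5D carry a protection that only iABM versus placebo has.

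**Working it through.** **1. Who is blinded to what**

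| Contrast | Patients blinded? | Therapists blinded? | Where used |
|---|---|---|---|
| iABM v placebo | Yes, by design | Yes, by design | Named in Trial design; not in the clinical ANOVAs |
| iABM v TAU-only | No | No | Economic evaluation |
| iABM v pooled controls | For half of the controls | For half of the controls | All clinical ANOVAs |

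That TAU-only patients and their therapists can tell the allocation is inferred from the procedures. The documents do not state it, but they describe nothing that would hide the absence of training.

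**2. Is every assessment online?** The Blinding section says yes. The Questionnaires section says the MATE at intake and end of treatment goes through the therapists. Both cannot be literally true. The intake MATE comes before allocation in the described sequence, so the end-of-treatment MATE is where therapist knowledge matters.

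**3. Share of open-label controls.** From the 50:25:25 allocation, TAU-only is 25/50 = 50% of the control arm.

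**4. The plan's own sample size.** Inputs from Sample size: medium effect (taken as d = 0.5), alpha 0.05 (taken as two-sided), power 0.80, 40% dropout.

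- The two-sample t-test needs 63.8, so 64 per arm, as stated.
- Total: 128/(1 − 0.40) = 213.3, against 213 stated. This reproduces.
- Completers: 213 × 0.60 × 0.50 = 63.9 on iABM, and 213 × 0.60 × 0.25 = 31.95 in each control condition, so about 64, 32 and 32.

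**5. Power of the blinded contrast.** The standardised distance is d/√(1/n₁ + 1/n₂).

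- Pooled, 64 v 64: 0.5/√(1/64 + 1/64) = 0.5/0.177 = 2.83, power 0.80.
- iABM v placebo, 64 v 32: 0.5/√(1/64 + 1/32) = 0.5/0.217 = 2.31, power about 0.63.

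**6. Illustration of bias.** Suppose TAU-only patients report b SD worse only because they know they have no training, and there is no true effect. TAU-only is half of the controls, so the pooled contrast shifts by b/2.

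| Assumed b (SD) | Pooled shift (SD) | Share of d = 0.5 | Chance of p < 0.05, 64 v 64 t-test |
|---|---|---|---|
| 0.2 | 0.1 | 20% | 8.7% |
| 0.4 | 0.2 | 40% | 20.2% |

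The values of b are assumptions; the documents give neither size nor direction. The last column describes a simple t-test at one time point, not the planned 4 × 2 repeated-measures ANOVA.

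**The case against.** The strongest reply is that the disputed sentence concerns researcher influence only. The section treats patients and therapists separately and limits their blinding to the two training conditions, so a careful reader can work out that TAU-only is open. This stands in part: a reader might infer that the protocol claims TAU-only patients are blinded, and it does not. What fails is the general conclusion about the outcome data, which come from all three arms.

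A second reply is that an add-on trial cannot hide the absence of training, and that TAU-only is there on purpose to estimate the effect of adding iABM to usual care. This stands in full. Neither the arm nor its use in the economic evaluation is an error; what needs correcting is the label.

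A third reply is that the bias is assumed. This also stands. A reader might infer that the main analysis has a false-positive rate of 9–20%, but the documents do not support that: the shift is hypothetical and the test differs from the planned one. No such rate can be attached to iABM versus TAU-only either, because the clinical analysis specifies no such test and the economic evaluation uses bootstrapping and acceptability curves.

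Finally, the odd-one-out task measures reaction time and is less exposed to self-report. It serves as a manipulation check, however, not as a primary outcome.

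**Conclusion.** The blinding statement is wrong as written, for two reasons that need no assumed numbers. Absence of researchers does not blind patient-reported outcomes in an arm that can tell its allocation, and the article itself says that not all assessments are online. The reach is definite: 25% of all patients, half of the controls in every clinical ANOVA, and the whole comparator in the economic evaluation. The size of any resulting bias is unknown; the 0.1–0.2 SD shift is an illustration that depends on an assumed 0.2–0.4 SD reporting difference.

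A reader might go further and conclude that no training effect may be claimed unless iABM beats placebo. The documents do not support that. The clinical analysis rests on the pooled contrast, for which the trial was sized at 0.80 power. Making success depend on a contrast with about 0.63 power would change the decision rule, with a real trade-off, and would go beyond correcting a description. The point calls for accurate wording and labelling and does not invalidate the design.

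**What to change.** - **Reconcile Blinding with Questionnaires.** State how the MATE is collected at intake, end of treatment and each follow-up, and what part the therapist plays.
- **Replace the general blinding claim.** Say that patients and therapists are blinded only between iABM and placebo, that TAU-only is open-label, and that online collection removes researcher influence but does not blind the patient.
- **Label the results.** Describe iABM versus pooled controls as partly open-label and the economic evaluation against TAU-only as open-label.
- **Report iABM versus placebo beside the pooled result.** Present it as the supporting blinded contrast, in line with the purpose given in Trial design, and state its power of about 0.63 at d = 0.5 with 64 v 32 completers. It should not be a condition for the main claim.

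The cost is a few sentences of text and one additional reported contrast, with no new data and no change to the sample size. The downside is that the trial's stated blinding becomes less favourable, and that the supporting contrast may be inconclusive at its lower power.

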### Data analyses

#### Clinical analysis

First, changes in attentional bias, as measured with the *odd one out task*, will be examined by using a 4 (within subjects: pre, post, FU1, FU2) × 2 (between subjects: TAU + iABM versus control conditions) repeated measure ANOVA, with attentional bias as dependent variable. To assess the validity of the main hypothesis, a 4 (within subjects: pre, post, FU1, FU2) × 2 (between subjects: TAU + iABM versus control conditions) repeated measure ANOVA will be conducted to examine the effects of the iABM intervention on substance use and craving, as measured with the MATE. In order to evaluate the effects of iABM intervention on rates of relapse, a Cox regression analysis will be conducted to model the time until relapse occur.

Further, changes in secondary physical and psychological complaints (depression, anxiety and stress) will be tested by a 4 (within subjects: pre, post, FU1, FU2) × 2 (between subjects: TAU + iABM versus control conditions) repeated measure ANOVA, based on the MATE. Missing data will be handled with multiple imputation.

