### Trial objective and hypothesis

The current study will investigate the effectiveness of a newly developed internet-based ABM (iABM) training as an add-on intervention to treatment as usual (TAU; consisting of protocolled CBT-based interventions), in alcohol and cannabis dependent outpatients. More specifically, the study will evaluate whether this new iABM training enhances treatment outcomes, and may be a cost-effective component that should be added to treatment in addiction care. The focus of the study is to examine the additional effects of iABM training on changes in substance use, craving, and relapse rates. Measurements of attentional bias will serve as a manipulation check for the efficacy of the current training to successfully modify attentional bias. This is important because only if the current iABM intervention is effective in modifying patients’ attentional bias it can be expected to have an impact on their substance use.

Based on this objective, we will test the hypothesis that patients who receive iABM intervention, compared to controls, will show less substance use, less craving, and lower relapse rates at post-measurement and 6 and 12 months after treatment. In addition, we will test if patients who received iABM intervention will show increased health and reduced physical and psychological complaints. Furthermore, we predict that these patients will show a reduction in health care usage 6 and 12 months after the intervention. Moreover, we predict that the effects on the individual and societal level will cause a decrease in societal costs that outweighs the additional costs of iABM intervention. Finally, we hypothesize that participants who show a stronger attentional bias and higher rates of craving before starting the ABM training will benefit most from this intervention.

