### Sample size

To find a difference between groups of medium effect size with a power of 0.8 at an alpha of 0.05, both the treatment and the control arm need to include 64 patients, as calculated with.

G*power 3.1.5. Dropout rates in regular addiction treatment are known to be approximately 20%. Given the 6 and 12 months follow-up measurements a dropout rate of 40% was calculated. Therefore, a total amount of 213 patients will be recruited.

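### The 4 × 2 repeated-measures ANOVA treats the pre-treatment value as an outcome, so its tests are less efficient than baseline-adjusted ones and the stated 0.80 power belongs to neither of them

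*Protocol article*

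**What the plan says.** Clinical analysis names the model that tests the main hypothesis: "To assess the validity of the main hypothesis, a 4 (within subjects: pre, post, FU1, FU2") × 2 repeated-measures ANOVA, iABM against the combined control conditions, with substance use and craving as outcomes. The same model is set for attentional bias and for depression, anxiety and stress. Baseline is one of the four outcome levels and no baseline covariate is named. Relapse is handled separately by Cox regression. On incomplete data the section says: "Missing data will be handled with multiple imputation".

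Trial objective and hypothesis predicts less substance use, less craving and "lower relapse rates at post-measurement and 6 and 12 months after treatment". The pre-treatment measurement is not among those time points.

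Sample size is set "To find a difference between groups of medium effect size with a power of 0.8 at an alpha of 0.05", so that "both the treatment and the control arm need to include 64 patients". It continues: "Given the 6 and 12 months follow-up measurements a dropout rate of 40% was calculated", and therefore "a total amount of 213 patients will be recruited". It gives no number of measurements and no correlation between them. Randomization allocates "1) 50% TAU + iABM, (2) 25% TAU + placebo condition and (3) 25% TAU-only", which is 1:1 for iABM against the pooled controls.

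**The concern.** A 4 × 2 ANOVA of this kind offers two tests involving group.

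- **Group main effect.** This compares the arms on the mean of all four measurements. One of the four precedes treatment, and randomised arms have no expected difference on it, so a quarter of the average carries no treatment effect.
- **Group × time interaction.** This asks on 3 df whether the arms change differently in any way. It has no single sign and is not itself an estimate of the difference at post, 6 or 12 months, which is what the hypothesis is about.

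The sample size appears to come from a third, simpler test. The stated 0.80 would then describe neither test the trial will run. The baseline value, which Table 2 shows is collected for these measures, would be spent as an outcome level instead of being used to reduce residual variance.

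**Working it through.** **1. Reproduce the stated sample size.** Inputs from Sample size: alpha 0.05 (two-sided assumed, since sidedness is not stated), power 0.80, medium effect taken as d = 0.5. A two-sided two-sample t-test (noncentral t) needs 63.77 per arm, rounded up to 64, with power 0.801. A one-sided test would need only 50 to 51. For dropout, 128/(1 − 0.40) = 213.3, matching 213. The document names no t-test; it is inferred because the figure matches and because power for either ANOVA test would need a correlation that is not given.

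**2. Set up the ANOVA tests.** Assumptions not in the documents: equal SDs scaled to 1, compound symmetry with correlation ρ, n = 64 evaluable per arm, and a constant effect of 0.5 SD at all three post-baseline visits. The group differences are δ = (0, 0.5, 0.5, 0.5), with mean 1.5/4 = 0.375.

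- *Main effect* (1 and 126 df): λ = (n/2) × 0.375² ÷ [(1 + 3ρ)/4] = 18/(1 + 3ρ).
- *Interaction* (3 and 378 df): λ = (n/2) × Σ(δ − 0.375)² ÷ (1 − ρ). The sum is 0.375² + 3 × 0.125² = 0.1875, so λ = 6/(1 − ρ).

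**3. Set up the baseline-adjusted tests.** The post-baseline covariance given baseline is A = S − ρ²J, where S is the 3 × 3 correlation matrix and J is all ones.

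- *Joint test of the three visits* (3 and 375 df): λ = (n/2) μ′A⁻¹μ = 24/[(1 − ρ)(1 + 3ρ)].
- *One visit* (1 and 125 df): λ = (n/2) × 0.5²/(1 − ρ²) = 8/(1 − ρ²).

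**4. Power from the noncentral F distribution** (λ in brackets):

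| ρ | ANOVA main effect | ANOVA interaction, 3 df | Adjusted joint, 3 df | Adjusted single visit |
|---|---|---|---|---|
| 0.3 | 0.86 (9.47) | 0.68 (8.57) | 0.96 (18.05) | 0.84 (8.79) |
| 0.5 | 0.76 (7.20) | 0.84 (12.00) | 0.97 (19.20) | 0.90 (10.67) |
| 0.7 | 0.67 (5.81) | 0.97 (20.00) | 0.99 (25.81) | 0.98 (15.69) |

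In each row the adjusted joint λ equals the sum of the two ANOVA values, apart from rounding (at ρ = 0.5, 7.20 + 12.00 = 19.20). Each ANOVA test therefore uses only part of the information that the adjusted test uses.

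**5. Other effect patterns at ρ = 0.5,** interaction against adjusted joint test, both 3 df:

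| Effect at post, 6, 12 months (SD) | Interaction | Adjusted joint |
|---|---|---|
| 0.5, 0.375, 0.25 (decaying) | 0.69 | 0.86 |
| 0, 0.25, 0.5 (late) | 0.80 | 0.86 |
| 0.5, 0, 0 (post only) | 0.84 | 0.86 |

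The matched adjusted test is higher each time, by an amount that depends on the pattern.

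**6. What a significant interaction can mean.** With effects of +0.4, 0 and −0.4 SD and ρ = 0.5, Σδ² = 0.32 and λ = 32 × 0.32/0.5 = 20.48. The interaction is significant with probability 0.98 although the average benefit is zero. An adjusted joint test has the same property, so the differences by visit must be reported whichever omnibus test is used.

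**The case against.** The interaction is a legitimate test. Under randomisation the baseline means are equal in expectation, so no interaction means no group difference at any of the three later visits. Primary and secondary outcome measures also frames effectiveness as change, which fits an interaction. This stands: the test is valid, and the dilution to 0.375 SD applies only to the main effect, which the article does not name as decisive. Which term decides may be settled in an analysis plan not shown here, so that silence is not counted against the protocol.

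A reader might set the interaction's 0.68 or 0.84 beside the 0.99 that a baseline-adjusted average of the three visits reaches at ρ = 0.3 or 0.5, and infer a very large loss. That compares a 3-df test with a 1-df test under the pattern most favourable to an average. For the late effect in step 5 the order reverses: interaction 0.80, adjusted average 0.59 at ρ = 0.5. The Discussion itself expects that benefit may appear only in the months after treatment.

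A reader might also infer that the trial is underpowered. The documents do not support this. The correlation is not given, and for a constant 0.5 SD effect the interaction passes 0.80 at ρ of 0.5 or more, while the main effect passes it at 0.3.

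Nor does the objection that repeated-measures ANOVA discards incomplete cases succeed, because multiple imputation is planned and the 213 already allows for 40% loss.

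**Conclusion.** The point holds as a mismatch and a loss of efficiency for substance use, craving, attentional bias and depression/anxiety/stress. The stated 0.80 is that of a two-group comparison at one time, and neither ANOVA test has that power except by coincidence of ρ. Like for like on 3 df with a constant 0.5 SD effect, baseline adjustment raises power from 0.68/0.84/0.97 to 0.96/0.97/0.99 at ρ = 0.3/0.5/0.7. The gain is clear at low to moderate correlation and small at 0.7. These sizes rest on compound symmetry, equal SDs, 64 evaluable per arm and the assumed effect pattern; that 64 came from a t-test is inferred. The ANOVA is not invalid, and relapse and the economic evaluation are not touched.

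**What to change.** - In Clinical analysis, replace the 4 × 2 ANOVA for these outcomes with a model of the post, 6- and 12-month values that has the baseline value as covariate and a condition × visit term. ANCOVA or a linear mixed model would serve, and either is compatible with the planned multiple imputation.
- Report the adjusted between-group difference, with confidence interval, at each of the three visits.
- Have the sponsor name the deciding contrast in advance: the joint test, the average over visits, or one named visit. This is a real trade-off. At ρ = 0.5 an adjusted 12-month contrast has power 0.90 for the late effect above but only 0.05 if the effect is confined to post, where the adjusted joint test has 0.86.
- In Sample size, name the test and restate the power for that contrast with its assumed correlation, preferably over a range.

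The cost is analysis wording and one power calculation. The baseline is already collected, so no extra patients, visits or measurements are needed.

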## Methods and design

### Trial design

The present study is a multicentre randomized controlled two-armed, parallel-designed trial with one treatment arm (iABM intervention) and a control arm, which will be divided into a placebo condition and a TAU-only condition (see Fig. 1). The inclusion of these two control conditions enables (1) the investigation of the effect of TAU + iABM intervention, related to TAU-only, and (2) the control for a possible placebo effect, by comparing the iABM condition with the placebo condition. The design of the study enables that iABM intervention, as well as the placebo condition, can be provided parallel to treatment as usual (TAU). Recruitment will take place in four addiction care centres in the Netherlands (*Iriszorg*, *Novadic-Kentron, Tactus Verslavingszorg and Verslavingszorg Noord Nederland*). There are two treatment intensities in the Dutch mental health care system. All participants who will be included in this study will receive the lower dose treatment, in which TAU consists of 350 to 750 min of protocolled CBT-based intervention in a specialized addiction care institution, including a 30% range of possible additional interventions, such as medication. Whether therapists make use of such additional intervention components depends on the severity of addiction and possible related problems of the patients. Patients who are ascribed to this intensity of treatment are expected to live relatively independent and to report less comorbidity. The additional effects of the iABM intervention will be tested directly after the end of TAU, which is also the end of the training, and 6 and 12 months later. For an overview of the planned timeline of the study, see Fig. 2.

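### Every clinical ANOVA pools placebo with TAU-only, so no clinical analysis isolates the specific iABM effect that the placebo condition was included to show

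*Protocol article*

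**What the plan says.** The Trial design section describes a two-armed trial whose control arm is split into a placebo and a TAU-only condition. It gives two reasons for the split. The first is "the investigation of the effect of TAU + iABM intervention, related to TAU-only". The second reason given there is "the control for a possible placebo effect, by comparing the iABM condition with the placebo condition".

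The Clinical analysis section specifies a 4 × 2 repeated-measures ANOVA for the main hypothesis, whose outcomes are substance use and craving: "2 (between subjects: TAU + iABM versus control conditions) repeated measure ANOVA will be conducted to examine the effects of the iABM intervention". The two-level between-subjects factor (iABM against the control conditions together) recurs for attentional bias, which is the manipulation check, and for depression, anxiety and stress. Relapse is to be analysed by Cox regression, with no comparison groups stated.

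The Sample size section works at the level of the two arms. Its target is stated as "To find a difference between groups of medium effect size with a power of 0.8 at an alpha of 0.05". From this it concludes that "both the treatment and the control arm need to include 64 patients". It then allows for attrition ("a dropout rate of 40% was calculated") and arrives at the recruitment figure: "a total amount of 213 patients will be recruited". The Randomization section allocates "1) 50% TAU + iABM, (2) 25% TAU + placebo condition and (3) 25% TAU-only".

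A single control condition serves as comparator in only one place. The Economic evaluation section compares iABM with TAU-only, and that evaluation runs only if iABM has first been shown effective.

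**The concern.** The two control conditions are not interchangeable. According to Participants and procedure, patients in both training conditions train daily for three weeks, then three times a week for three weeks, then weekly until TAU ends. They get reminders and researcher contact when sessions are missed, and their therapists ask about training and counsel them if it lapses. TAU-only patients have no training to which any of this could attach. According to Blinding, therapists and participants are blinded only as between the two training conditions, so TAU-only is open.

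Averaging the two controls therefore mixes two questions: whether attentional bias modification works beyond a sham training, and whether adding any training to TAU helps. A difference from the average can arise entirely from the second. The Background section itself describes an internet-delivered ABM study in which the drop in drinking also appeared in the placebo group and so could not be credited to the intervention. The planned test could not reliably recognise that pattern here.

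A positive result also has consequences within the plan: it triggers the economic evaluation, and a proven effect leads to iABM being offered to control patients.

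**Working it through.** **1. The plan's own figure.** Inputs from Sample size: medium effect (no number given; d = 0.5 assumed), power 0.80, alpha 0.05 (two-sided assumed). A two-sample t-test with 1:1 allocation, solved with the noncentral t distribution, needs 63.77 per arm, so 64. Power at 64 v 64 is 0.801. A one-sided test would need only 51, which does not match. Inflating for dropout: 128 / (1 − 0.40) = 213.3, against 213 stated. The figures reproduce for iABM versus the pooled control.

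**2. What the pooled contrast estimates.** The two controls are allocated equally (25% each), so the pooled difference is

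μ(iABM) − ½[μ(placebo) + μ(TAU-only)] = ½[Δ(placebo) + Δ(TAU-only)],

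where each Δ is iABM minus that control. If iABM has no specific effect, Δ(placebo) = 0. If any training gives a benefit of s over TAU-only, Δ(TAU-only) = s, and the pooled difference is s/2 rather than zero.

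**3. How often that favours iABM.** The documents give no value for s, so a range is assumed. Simulation: iABM N(s, 1) with n = 64, against 32 placebo N(s, 1) plus 32 TAU-only N(0, 1), two-sided 0.05, counting significant results in favour of iABM.

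| Assumed s (SD) | True pooled difference | Pooled test favours iABM |
|---|---|---|
| 0 | 0 | 2.5% |
| 0.3 | 0.15 | about 13% |
| 0.5 | 0.25 | about 28% |
| 1.0 | 0.50 | about 77% |

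In the same simulations, iABM versus placebo favours iABM in about 2.5% of trials whatever the value of s. That is the property an attribution claim needs.

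**4. Power of the single-control contrasts.** With 213 recruited at 2:1:1 and 40% dropout in every condition, about 64 / 32 / 32 remain. The noncentrality is δ = d / √(1/n₁ + 1/n₂). For 64 v 64 it is 0.5 / √(1/64 + 1/64) = 2.83; for 64 v 32 it is 0.5 / √(1/64 + 1/32) = 2.31. At d = 0.5 and two-sided 0.05:

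| Dropout | iABM v one control | Power |
|---|---|---|
| 40% (planned) | 64 v 32 | 0.63 |
| 20% (figure given for regular treatment) | about 85 v 43 | 0.75 |
| none | about 106 v 53 | 0.84 |

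At 64 v 32 the effect detectable with power 0.80 is d = 0.61. At alpha 0.025 the power is 0.51.

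**The case against.** The strongest reply is that the pooled plan is coherent in itself. The trial is called two-armed, the hypothesis is worded against controls in general, the sample size is set per arm, and 50/25/25 allocation makes the pooled contrast 1:1. All of that stands. A reader might infer that the sample size is wrong or that the protocol claims 0.80 for the pairwise comparisons. It does neither: 64 and 213 reproduce for the contrast that is sized.

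A reader might also take 13% and 28% as an inflated type I error. They are not. In those scenarios iABM truly beats TAU-only, and truly beats the average of the two controls, so rejecting is correct for the test as stated. It would even be the right answer to the first purpose in Trial design. The error lies in reading the result as an effect of attentional bias modification.

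Nor is it right that neither comparison appears anywhere. The economic evaluation uses TAU-only, and the Cox groups are simply unstated. But the economic comparison is conditional, is not a test of efficacy and leaves placebo out.

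Two further replies carry some weight. A separate analysis plan could add pairwise contrasts, and their absence from an article would not by itself be a finding. Here, however, the article fixes the main-hypothesis test as pooled, in conflict with its own reason for having two controls. Attentional bias as a manipulation check also gives some protection against misattribution, but that ANOVA is pooled as well.

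**Conclusion.** The point holds as a mismatch between Trial design and Clinical analysis. The placebo condition is included to control for a placebo effect by direct comparison with iABM, and no specified clinical analysis makes that comparison. Followed as written, the plan could credit iABM with a benefit that arises only because TAU-only patients have no training contact. How often depends on a non-specific effect that the documents do not quantify: about 13% of trials at an assumed 0.3 SD and 28% at 0.5 SD.

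The sample size needs no correction, only a statement of which contrast it covers. The 0.63 for each single-control contrast assumes d = 0.5, two-sided 0.05, a simple two-group t-test on completers and equal 40% dropout. The protocol gives no repeated-measures correlation, and the planned repeated-measures model with multiple imputation would shift the absolute values. On a common basis, a contrast with half the control patients still has less power than the pooled one.

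**What to change.** In Clinical analysis:

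- Replace the two-level factor with a three-level condition factor.
- The pooled contrast may stay as the powered test. Follow it, in a pre-specified order, by iABM versus placebo and then iABM versus TAU-only, each tested at 0.05 only if the one before it is significant.
- Apply the same contrasts to the attentional-bias, Cox and secondary models, and name the Cox groups.
- State that a claim that attentional bias modification itself works will be made only if iABM versus placebo supports it.

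In Sample size, state that 0.80 applies to the pooled contrast, and that each single-control contrast taken alone has about 0.63 under the assumptions above (about 0.75 at 20% dropout, 0.84 with none).

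The cost is wording and a less favourable stated power; no extra patients are needed. The trade-off should be accepted openly. Dropping the pooled contrast in favour of two primary pairwise tests would give up the only contrast powered at 0.80. Restoring 0.80 for each pairwise contrast at alpha 0.05 would take 96 + 48 + 48 = 192 completers, or 192 / 0.6 = 320 recruited. Under the fixed order, a failed placebo contrast also leaves iABM versus TAU-only descriptive.
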